**Introduction**

**Background and rationale**

Hypothyroidism is a common endocrine disorder diagnosed with low levels of thyroid hormones, mainly due to the lack of thyroid hormone production by the thyroid gland or, secondarily, caused by the lack of thyroid stimulating hormone (TSH) from the anterior pituitary gland or thyrotropin-releasing hormone (TRH) from the hypothalamus (1, 2). Due to the vital role of thyroid hormones in metabolism, the clinical manifestations of this disease include fatigue, difficulty in concentration and memory, constipation, weight gain and loss of appetite, depression, slow heart rate and hypercholesterolemia (3). The prevalence of hypothyroidism is higher in women, but after the age of 60, its prevalence in men and women becomes ~10% (4). The incidence of hypothyroidism is reported to be 1-2% among two-thirds of the world's population living in communities with adequate consumption of iodine (5). The gold standard for treatment of hypothyroidism is currently dose-adjusted levothyroxine (6), although side effects such as neurological alterations have been reported from this drug (7). Because of the disease itself and its many complications, a great economic burden is imposed on the family and society (8), hence, the use of non-pharmacological methods with less complications and costs, in addition to the common treatment can be beneficial to the health care system and hypothyroid patients.

Probiotics are living non-pathogenic micro-organisms that, when received in sufficient doses, contribute to the health of the host; and prebiotics are degraded by these beneficial micro-organisms and enhance their growth or activity (9). The combination of probiotics and prebiotics with synergistic effects is called “synbiotic” (10). Modulating gut microbiota by synbiotic supplementation has shown to have beneficial health effects in various disease and conditions (11, 12).

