**Eligibility criteria**

Inclusion criteria

Women or men (25-55 years old) with subclinical hypothyroidism (elevated TSH level and a normal or low free T4 level) for at least a year, and BMI less than 35 who are being treated by levothyroxine. Voluntary written informed consent for all patients is mandatory before any study related procedures.

Exclusionary criteria

The participants must not have any of the following: lactating or pregnant; History of taking probiotic or synbiotic supplements in the last three months; Smoking or alcohol consumption; Taking appetite suppressants such as antibiotics; Use of antibiotics and any medications that interact with synbiotics; Gastrointestinal diseases such as stomach ulcers, diarrhea or constipation etc. for three months before or during the intervention; unwillingness to continue cooperation, non-compliance during the intervention, or no signed informed consent. Participants will also be excluded in case of providing incomplete questionnaires (more than 40% of the dietary questionnaire is incomplete), catching infectious diseases such as Covid-19 during the study, occurrence of pregnancy, undergoing surgery, occurrence of a change in the dose or type of medication, consumption of foods enriched with probiotics (e.g. probiotic yoghurt) during the study.

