**Interventions**

Therapeutic effect of probiotics and synbiotics on the serum level of thyroid hormones have been assessed with different species and doses of bacteria and follow-up duration between 4 to 12 weeks (30, 31). Previous trials have used either different species of Lactobacillus genus (32) or a combination of Lactobacillus and Bifidobacterium (21, 29-31, 33). The microbial load of the supplements varied between 10^7^ to 10^10^ CFU/g. Inulin, fructo-, and/or galacto- oligosaccharide have been used as the prebiotic component of synbiotic (21, 30, 32). We decided to conduct this intervention with synbiotic instead of probiotic, since the synergistic interaction of probiotic and prebiotic can more effectively improve the microbial composition of the gut and maintain the intestinal microbial balance (10). The duration of intervention was decided to be 10 weeks, as the previous trials with less duration of intervention reported no significant effect of synbiotic or probiotics on serum level of thyroid hormones and BP (29, 33). A comprehensive meta-analysis also showed that less than 8 weeks supplementation with probiotics had no significant effect on BP (34). The synbiotic supplement (Familact, 500 mg) that will be used in this study contains Lactobacillus casei, Lactobacillus acidophilus, Lactobacillus rhamnus, Lactobacillus bulgaricus, Bifidobacterium Breve, Bifidobacterium Longum, Streptococcus thermophilus plus fructo-oligosaccharide with microbial population of 10^9^ CFU/g. Placebos contain lactose, magnesium stearate, talc, and silicon dioxide and will be made in the same shape, color, odor and taste as the synbiotic supplements. Zist-takhmir Pharmacutical company will provide the synbiotic and placebo capsules. All participants will receive a capsule (Synbiotic supplement or placebo) to be consumed with lunch, daily. Also, the participants will receive appropriate recommendations regarding diet and PA. The recommendations will include: to follow a hypo-caloric diet; to avoid excessive intake of high-fat products (whole dairy products, poultry fat (the skin on chicken), processed meat, butter, cream, ice cream, and palm oil); to avoid excessive sugar intake (candy, soda, syrups, sugar-loaded desserts, caramels, chocolate); to increase PA by walking or cycling for at least 20 minutes for at least 5 days a week.

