The supplements will be delivered to the participants at the first appointment and the supplement boxes will be collected at the end of the intervention by the outcome assessor. To recall the participants of the supplements intake and follow the routine recommendations, we will use telephone or online applications such as WhatsApp or Telegram. If supplements intake is missed at lunch, patients will be advised to take them during the same day. They will also be asked to report any complications or adverse event during the study period. The intervention will be discontinued in case of severe and serious complications following the supplementation.

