**Outcomes**

Schedule of outcome assessment is represented in Figure 2. The primary outcomes include serum levels of TSH and fT4. The secondary outcomes are BP, quality of life, and depression. The information on anthropometric indices, PA, and dietary intake will be collected to control the potential confounders and covariates. The primary and secondary outcomes will be conducted at baseline and the end of the study (10th week) for all participants and change from baseline will be reported. Adherence will be checked every week.

**Figure 1**. Flow chart of the study design.

Eligible hypothyroid adults (women/men) with written informed consent will be recruited from Baqiyatallah hospital and will be enrolled in this RCT (n=56)

Randomize to two parallel treatment groups for 10 weeks (70 days):

1) synbiotic supplement (n= 28)

2) placebo (n= 28)

1

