**Implementation**

The treatment codes will remain with the staff until the final data analysis and/or an emergency situation. After checking the inclusion and exclusion criteria and baseline measurements, each participant will be given a supplement box.

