**Harms**

Information about adverse events and other unintended effects of trial intervention will be collected during the weekly checks through the social media. Participants will also be provided with the number of the researcher and will be asked to make contact in case of adverse events.

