**Ancillary and post-trial care**

No ancillary and post-trial care would be provided to the patents unless a persistent complication (e.g. gastro-intestinal) exist following the intervention.

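### The gastrointestinal exclusion also runs during the intervention, with no severity or cause threshold, so a randomized participant can be excluded for a mild bowel event that the capsule may cause

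*Protocol*

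**What the plan says.** The Protocol's Eligibility criteria list, among the exclusions, "Gastrointestinal diseases such as stomach ulcers, diarrhea or constipation etc. for three months before or during the intervention". No grade, duration or cause is attached. The next sentence of that section goes on to further on-study events for which participants will also be excluded, so the list serves both as an entry screen and as a removal rule.

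Four other places bear on how this item works:

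- **Implementation** puts the eligibility check before the capsules are handed over: "After checking the inclusion and exclusion criteria and baseline measurements, each participant will be given a supplement box".
- **Interventions** sets a different bar for stopping treatment: "The intervention will be discontinued in case of severe and serious complications following the supplementation".
- **Outcomes** says: "The primary and secondary outcomes will be conducted at baseline and the end of the study (10th week) for all participants". Data collection methods repeats this.
- **Harms** provides for reporting without a severity limit: "Information about adverse events and other unintended effects of trial intervention will be collected during the weekly checks through the social media".

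Three further statements concern what might trigger the item. Interventions describes the synbiotic as live bacteria plus fructo-oligosaccharide, and of the comparator it says: "Placebos contain lactose, magnesium stearate, talc, and silicon dioxide". Ancillary and post-trial care offers no care after the trial "unless a persistent complication (e.g. gastro-intestinal) exist following the intervention". Background and rationale states that "the clinical manifestations of this disease include fatigue, difficulty in concentration and memory, constipation, weight gain and loss of appetite".

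**The concern.** An exclusion that acts after randomization is harmless to the comparison only if its trigger is unrelated to the assigned arm and to the outcome. Here neither can be taken for granted. The two capsules differ in content that reaches the gut, the intervention is meant to change the gut microbiota, and the Protocol itself foresees gastrointestinal complications. Constipation is also named as a feature of the disease whose hormones are the primary outcome.

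If bowel events occur at different rates in the two arms, and those who have them differ in TSH or fT4 change from those who do not, removing them makes the remaining groups non-comparable. Blinding prevents deliberate removal from one arm, but it does not equalise event rates. Extra recruitment does not cure the problem either, because it is bias and not loss of precision.

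The rule is also unworkable as it stands. Staff who learn of mild diarrhea in week 3 find one section that excludes the participant, one that lets treatment continue, and one that expects a week-10 measurement.

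**Working it through.** **1. When the item can act.** Criteria are checked before the box is given (Implementation). The part of the item that refers to the intervention period can therefore apply only to people already assigned. The three-month figure cannot serve as a minimum duration on study, because the intervention lasts 10 weeks (Interventions).

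**2. Which section governs a non-severe event.**

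| Section | Non-severe diarrhea or constipation on study |
| --- | --- |
| Eligibility criteria | Ground for exclusion |
| Interventions | Below the bar for stopping treatment |
| Outcomes; Data collection methods | Week-10 outcomes measured in all participants |
| Harms | Recorded |

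No section states an order of precedence or says what exclusion means for follow-up.

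**3. The only related figure in the plan.** Sample size gives 24 required per group, a 15% allowance and 28 per group. Multiplying, 24 × 1.15 = 27.6, which rounds up to 28. (Dividing, 24/0.85 = 28.2, gives 29.) The allowance is 28 − 24 = 4 per group.

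**4. Illustrative size.** The Protocol gives no gastrointestinal event rate, so every input here is assumed except 28 and 4. Let p be the fraction removed in an arm, and let δ be the removed-minus-retained difference in TSH change, in SD units. The mean of the full arm equals the retained mean plus p × δ, so the between-arm difference shifts by |p₁δ₁ − p₀δ₀|. With the same δ in both arms this is |p₁ − p₀| × δ. The standard error of the retained comparison is √(1/n₁ + 1/n₀), in SD units.

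- 1 versus 4 removed: 3/28 = 0.107; SE = √(1/27 + 1/24) = 0.281.
- 0 versus 4 removed: 4/28 = 0.143; SE = √(1/28 + 1/24) = 0.278.

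The last column is the rejection rate of a two-sided 5% t-test with zero true effect (noncentral t, df = n₁ + n₀ − 2, noncentrality = shift/SE).

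| Removed | δ (SD) | Shift (SD) | Shift/SE | False-positive rate |
| --- | --- | --- | --- | --- |
| 1 vs 4 | 0.5 | 0.054 | 0.19 | 5.4% |
| 1 vs 4 | 1.0 | 0.107 | 0.38 | 6.6% |
| 0 vs 4 | 0.5 | 0.071 | 0.26 | 5.7% |
| 0 vs 4 | 1.0 | 0.143 | 0.51 | 8.0% |

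Equal removals give zero shift only if δ is the same in both arms. With 2 versus 2 removed and δ of +0.5 and −0.5, the shift is (2/28) × 1.0 = 0.071 SD.

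**5. Why there is no conversion to mIU/L.** Sample size states an SD of 0.09 mIU/L and a target difference of 0.28 mIU/L. That is 0.28/0.09 = 3.1 SD, which needs about 3 patients per group. To obtain 24 per group for 0.28 at 80% power, the standardized difference must be about 0.826, so the SD would be 0.28/0.826 ≈ 0.34. The stated SD is therefore not a safe basis for conversion.

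**The case against.** The strongest counter-argument is that the damage is inferred. A reader might conclude that an excluded participant is never sampled at week 10. No section says so, and Outcomes says the opposite for all participants. Exclusion could mean stopping the capsules, leaving follow-up, or leaving the analysis. Only if it ends follow-up is the sample lost; otherwise what remains is who is analysed, which an analysis plan may settle. This stands, and it is why the point is put conditionally. What does not go away is the conflict between sections and the open meaning of a rule that staff must apply.

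Second, the item speaks of diseases and names ulcers, so a passing loose stool may not have been meant. That is fair as a reading of intent. Yet diarrhea and constipation are named without grading and the list is open-ended, so the broad reading is available.

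Third, the causal routes are only plausible. The Protocol gives no event rates and does not say that they differ by arm. The disease route is narrow, because entrants take levothyroxine and must have had no constipation in the preceding three months. This too stands, and it limits how firmly any size can be stated.

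Fourth, the investigators have a possible reason for the rule: Background and rationale says that gut bacterial overgrowth can reduce absorption of oral thyroxine, so intercurrent gut illness could disturb TSH and fT4. That is a genuine cost of retention. It does not justify removing people for an event that may itself follow from the assigned capsule.

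Finally, the same list contains other on-study exclusions that could be questioned in the same way. This point is confined to the gastrointestinal item.

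**Conclusion.** The concern holds as a defect in the stated rule. As written, a randomized participant can be excluded for a non-severe bowel event that may depend on the assigned capsule and, to a limited extent, on the disease. The rule conflicts with the stopping criterion in Interventions and with the week-10 commitment in Outcomes and Data collection methods. If exclusion ends follow-up, the TSH and fT4 comparison can be biased, and the loss cannot be repaired afterwards.

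The size is unknown. The illustrative range is modest, at most about half a standard error. It rests on three assumptions together: uneven removals that use one arm's whole loss allowance, a 0.5 to 1.0 SD difference between removed and retained participants, and no week-10 data from those removed. The direction cannot be predicted.

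Two stronger readings are not supported. The documents do not show that samples will in fact be lost or that the result will be biased. Nor do they show that harms go uncollected, since adverse events of any severity are gathered weekly. The change should be made because it is cheap and the ambiguity is real; confidence in any practical effect is moderate.

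**What to change.** - **Eligibility criteria:** limit the gastrointestinal item to the three months before entry.
- **Interventions:** state that an on-study gastrointestinal event, whether or not related to the supplement, may lead to stopping the capsules on clinical grounds. This also covers unrelated illness such as an ulcer. The clinical grounds remain with the investigators and the ethics committee.
- **Same place:** state that the participant is not removed from the trial, still attends the week-10 assessment described under Outcomes, and stays in the harms report.

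The cost is a short wording amendment with ethics committee approval, as Protocol Amendments requires. It needs no additional patients or staff, and no visit beyond the week-10 visit already planned.

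The downside is that some participants who are off capsules, or whose gut illness may disturb levothyroxine absorption, stay in the data and add some noise or dilution. A supportive analysis without them can be reported alongside the main one.

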**Sample size**

The sample size was calculated with G-power software version 3.1.9.2. To calculate the sample size, the study of Talebi et al. (29) was used, which was an 8-week clinical trial with two parallel groups. The sample size was calculated considering the probability of the first type error equal to 0.05 (α = 0.05, significance), and the probability of the second type error equal to 0.80 (β = 0.2, power). In this study, the mean change ± standard deviation of placebo and synbiotic groups regarding TSH levels after 8 weeks of intervention were 0.08 ± 0.09 mIU/L and 0.028 ± 0.09 mIU/L, respectively. In this study, in order to observe 0.28 mIU/L difference in serum TSH levels between the two groups at the end of the study, a sample size of 24 patients in each group is required. According to an expected 15% loss to follow-up, the final sample size included in each group will be 28 patients.

[figure not shown]

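### The exclusion list removes randomised participants for events after allocation, some of which may depend on treatment or outcome, so the randomised comparison can be biased

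*Protocol*

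**What the plan says.** Under Eligibility criteria, one exclusion list covers both entry and conduct. It includes "Gastrointestinal diseases such as stomach ulcers, diarrhea or constipation etc. for three months before or during the intervention" and "unwillingness to continue cooperation, non-compliance during the intervention, or no signed informed consent". It continues with "Participants will also be excluded in case of providing incomplete questionnaires", the threshold being more than 40% of the dietary questionnaire missing. The same sentence adds "catching infectious diseases such as Covid-19 during the study, occurrence of pregnancy, undergoing surgery" and "occurrence of a change in the dose or type of medication, consumption of foods enriched with probiotics (e.g. probiotic yoghurt) during the study".

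Other sections that bear on this:

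- **Implementation:** the supplement box is handed over only after the eligibility check and baseline measurements. Anything arising during the intervention therefore follows allocation.
- **Outcomes** and **Data collection methods:** primary and secondary outcomes are assessed at baseline and week 10 in every participant.
- **Statistical methods:** between-group comparison by ANCOVA. Nothing there, or elsewhere, says that an excluded participant's data are retained.
- **Sample size:** 24 per group, raised to 28: "According to an expected 15% loss to follow-up".
- **Ancillary and post-trial care:** no care after the trial "unless a persistent complication (e.g. gastro-intestinal) exist following the intervention".

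**The concern.** Randomisation protects the comparison only while the groups analysed are the groups randomised. Removing people for something that happened afterwards is harmless if the event is unrelated to treatment and outcome. Several listed events may not be.

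- **Medication change.** Every participant takes levothyroxine and is enrolled with raised TSH, and TSH and FT4 are the primary outcomes. A levothyroxine change, which the wording covers, may be a response to thyroid status. The Background also says that gut bacteria can affect absorption of oral thyroxine, so if the hypothesis is right the need for a change could differ by arm.
- **Gastrointestinal disease during the intervention.** The protocol itself foresees gastrointestinal complications after the supplement, yet diarrhoea or constipation in that period is a ground for exclusion.
- **Non-compliance and unwillingness to continue.** Either can follow from poor tolerability or from feeling no benefit.
- **Incomplete dietary form.** This has no bearing on whether a TSH or FT4 value is valid, but it removes the participant.

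At stake are the validity of the primary comparison and the number left to analyse. If week-10 samples are not taken from excluded participants, no later analysis plan can recover them.

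**Working it through.** **1. Timing.** Eligibility and baseline checks come first and the box second (Implementation). So events described as occurring during the intervention or the study are post-randomisation exclusions.

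**2. Internal consistency.** Eligibility criteria excludes participants with these events; Outcomes and Data collection methods measure every participant at week 10. Both cannot be followed if exclusion means leaving the trial, and the protocol does not say whether it means leaving treatment, follow-up or analysis.

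**3. Numbers.** The stated step is 24 per group with 15% loss. Dividing, 24 / 0.85 = 28.2 (29 if rounded up); multiplying, 24 × 1.15 = 27.6, which rounds to the stated 28. The reserve is 28 − 24 = 4 per arm. A fifth loss in an arm, from dropout or exclusion, leaves 23. I take the 24 as stated here.

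**4. When bias arises (illustration; rates and correlations are assumptions).** Take change scores in SD units, N(0,1) in both arms, so there is no true effect. A participant is excluded when a latent score, correlated ρ with the outcome, exceeds a cut-off c chosen to give the arm's exclusion rate. The mean among those retained is −ρ·φ(c)/Φ(c), so

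bias (synbiotic − placebo) = ρ·[φ(c_P)/Φ(c_P) − φ(c_S)/Φ(c_S)].

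For 20% and 10%: φ/Φ = 0.280/0.80 = 0.350 and 0.1755/0.90 = 0.195; the difference is 0.155, times 0.5 = 0.08 and times 0.8 = 0.12. A simulation of 40,000 trials with 28 per arm gave:

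| Excluded, placebo / synbiotic | Bias in SD (ρ = 0.5 to 0.8) | Two-sided type I error |
|---|---|---|
| 15% / 15% | 0.00 | about 5% |
| 20% / 10% | 0.08 to 0.13 | 5.8% to 7.8% |
| 15% / 0% | 0.14 to 0.22 | 7.6% to 12.4% |
| 25% / 5% | 0.16 to 0.25 | 8.3% to 15.0% |

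Positive values make synbiotic look worse on TSH. Swapping the rates reverses the sign. The 20%/10% row averages 15% overall, so bias can occur without total losses exceeding the planned allowance.

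**5. With a true effect (illustration).** Let the true difference be −0.5 SD, and exclude anyone whose change exceeds a common cut-off.

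- Cut-off +1 SD: losses 15.9% placebo and 6.7% synbiotic. Retained means are −0.288 and −0.5 − 0.139 = −0.639; the estimate is −0.35 (30% smaller).
- Cut-off +0.5 SD: losses 30.9% and 15.9%. Retained means are −0.509 and −0.5 − 0.288 = −0.788; the estimate is −0.28 (44% smaller).

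This shows the mechanism only. The protocol schedules TSH at baseline and week 10 alone, so a change score could not drive exclusion this directly.

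**The case against.** The strongest reply has four parts.

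- **Exclusion is undefined, and outcomes are planned for everyone.** It is true that the text does not say from what participants are excluded. But the rule stands in the list of exclusion criteria, where the natural reading is removal from the trial, and nothing says otherwise. The conflict has to be resolved, not assumed away.
- **TSH is not measured between baseline and week 10.** This stands. A dose change prompted by the baseline value reflects a pre-treatment measurement, which randomisation balances on average. Changes prompted by tests or symptoms outside the trial remain possible, at a frequency the protocol does not give. It limits the medication-change argument and makes step 5 hypothetical. It does not touch non-compliance, gastrointestinal complaints or dietary forms.
- **An analysis plan may define the analysis set.** Agreed: the protocol's silence on intention-to-treat is not the finding. The finding is the exclusion rule that the protocol does fix, together with the risk that the data are never collected.
- **Not every event is suspect.** Pregnancy, surgery and probiotic foods have no evident link to allocation in a blinded trial. The case rests mainly on medication change, gastrointestinal disease and non-compliance.

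A reader might also infer that the rule hides poor tolerability. The documents do not support that: the Interventions section, the weekly follow-up in Figure 1 and the Harms section all provide for collecting complications, and nothing says that reports from excluded participants are discarded.

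**Conclusion.** The point holds as a risk built into the protocol's wording. Followed as written, the rule can leave a comparison of selected participants, and no passage prevents this. A reader might go further and conclude that the comparison is biased. That is not shown: with equal outcome-related exclusion in both arms and no treatment effect the bias is zero, and the rates by arm that would settle size and direction are not given. The figures of 0.08 to 0.25 SD under no effect, and 30% to 44% attenuation under a −0.5 SD effect, rest wholly on assumed rates, correlations and cut-offs.

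On numbers, the firm statement is conditional: the evaluable group falls below 24 only if dropout and exclusions together exceed 4 of 28 in an arm. A reader might want to turn this into a loss of power, but the protocol states no standardised effect. One obtained by solving backwards from 24 per group would not be the planned one, so no power figure is offered.

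It should be settled before enrolment because uncollected week-10 outcomes cannot be restored.

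**What to change.** - Limit the eligibility list to conditions present before randomisation, and move the later events to a separate paragraph.
- Reconcile that paragraph with Outcomes and Data collection methods: seek week-10 TSH, FT4 and secondary outcomes from every randomised participant, whatever happened after allocation. This concerns data collection only; whether a participant continues the capsules is a separate clinical matter.
- Make the primary analysis all randomised participants as allocated.
- Do not drop TSH or FT4 data because a dietary form is incomplete.
- Record and report each listed event by arm.
- Keep the present exclusion rule only to define a per-protocol sensitivity analysis.

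The cost is revised wording, one additional analysis and the effort of bringing back participants who stopped. Including non-adherent participants may dilute the estimated effect somewhat; the per-protocol analysis shows by how much the two differ.
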